# Usability, Perceived Usefulness, and Shared Decision-Making Features of the AFib 2gether Mobile App: Protocol for a Single-Arm Intervention Study

**DOI:** 10.2196/21986

**Published:** 2021-02-24

**Keywords:** shared decision making, mobile health, stroke risk, anticoagulation risk, anticoagulation education, atrial fibrillation, anticoagulation therapy, anticoagulation, atrial flutter, mobile phone

## Abstract

**Background:**

The Centers for Disease Control and Prevention has estimated that atrial fibrillation (AF) affects between 2.7 million and 6.1 million people in the United States. Those who have AF tend to have a much higher stroke risk than others. Although most individuals with AF benefit from anticoagulation (AC) therapy, a significant majority are hesitant to start it. To add, providers often struggle in helping patients negotiate the decision to start AC therapy. To assist in the communication between patients and providers regarding preferences and knowledge about AC therapy, different strategies are being used to try and solve this problem. In this research study, we will have patients and providers utilize the AFib 2gether app with hopes that it will create a platform for shared decision making regarding the prevention of stroke in patients with AF receiving AC therapy.

**Objective:**

The aim of our study is to measure several outcomes related to encounters between patients and their cardiology providers where AFib 2gether is used. These outcomes include usability and perceived usefulness of the app from the perspective of patients and providers. In addition, we will assess the extent and nature of shared decision making.

**Methods:**

Eligible patients and providers will evaluate the AFib 2gether mobile app for usability and perceived usefulness in facilitating shared decision making regarding understanding the patient’s risk of stroke and whether or not to start AC therapy. Both patients and providers will review the app and complete multiple questionnaires about the usability and perceived usefulness of the mobile app in a clinical setting. We will also audio-record a subset of encounters to assess for evidence of shared decision making.

**Results:**

Enrollment in the AFib 2gether shared decision-making study is still ongoing for both patients and providers. The first participant enrolled on November 22, 2019. Analysis and publishing of results are expected to be completed in spring 2021.

**Conclusions:**

The AFib 2gether app emerged from a desire to increase the ability of patients and providers to engage in shared decision making around understanding the risk of stroke and AC therapy. We anticipate that the AFib 2gether mobile app will facilitate patient discussion with their cardiologist and other providers. Additionally, we hope the study will help us identify barriers that providers face when placing patients on AC therapy. We aim to demonstrate the usability and perceived usefulness of the app with a future goal of testing the value of our approach in a larger sample of patients and providers at multiple medical centers across the country.

**Trial Registration:**

ClinicalTrials.gov NCT04118270; https://clinicaltrials.gov/ct2/show/NCT04118270

**International Registered Report Identifier (IRRID):**

DERR1-10.2196/21986

## Introduction

Atrial fibrillation (AF) and atrial flutter occur in epidemic proportions in the United States [1-4]. The Centers for Disease Control and Prevention estimates that AF affects between 2.7 million and 6.1 million people in the United States [5]. Anticoagulation (AC) is the mainstay of therapy, but many patients are reluctant to start taking anticoagulants [6]. Patients who have a diagnosis of AF generally have a higher risk of stroke than the general population [7]. Even among those who do start AC therapy, many do not persist with the treatment after bleeding or other setbacks. Providers also struggle with balancing the risks and benefits of AC therapy. Being able to determine an optimal decision for each patient is a valuable goal in stroke prevention. Shared decision making has been recommended by the American Heart Association (AHA) and other professional societies as a way to arrive at an optimal decision, but the usability and perceived usefulness of conducting shared decision making via an app visit are unclear [8].

Conducting shared decision-making visits will require several changes from standard provider-patient interactions. Shared decision-making visits will help patients and providers make the best choice in therapy that will fit into a patient’s life. Firstly, providers do not always draw attention to the fact that there is a decision to be made and may make the decision for the patient without soliciting the patient’s preferences. Secondly, providers do not always inquire about the patient’s preferred treatment approach, which can create a barrier for shared decision making. It is also possible that providers may not be knowledgeable or confident in managing AF patients with the most recently published guidelines and the advent of direct oral AC therapy (ie, modern AF management). Conducting AF management through a shared decision-making process may help in overcoming the above limitations. Currently, it is unknown how best to operationalize shared decision making around AC therapy for AF.

Shared decision-making tools can help patients make informed decisions with less conflict [9]. The AFib 2gether mobile app, which was developed by Pfizer Inc in consultation with a cardiologist (DM), is one potential approach for operationalizing shared decision making around AC therapy for AF. The app can provide a platform for a patient to determine their risk of stroke and identify items for discussion at an upcoming visit with their provider. The app was designed to support collaboration during patient visits, which allows for the app to provide a high-level overview of AF and AC therapy and to prepare patients to have the tools needed to ask questions of their providers. The provider can review the answers given by the patient’s app as well as any questions the patient solicited in the app for discussion prior to the visit. The goal is that this interaction will help the patient make a more informed decision by helping them become more engaged in their health status and improve their stroke prevention management related to AF. We have not previously tested the app with patients and providers for usability and perceived usefulness for clinical encounters. Therefore, we describe herein our protocol for testing the app in a clinical setting, including measurement of the usability of the app and its usefulness during clinical appointments between patients with AF, who are not currently prescribed AC therapy, and their cardiology providers. We also propose a measurement of the extent and nature of shared decision making that occurs through audio-recording the encounters facilitated by our app.

## Methods

### Study Aims

The aim of the AFib 2gether research study is to measure the usability and perceived usefulness of the shared decision-making mobile app AFib 2gether from the perspective of patients and providers. We will also measure patient AC status by chart review 6 months after their shared decision-making visit to see if patients started AC therapy. Finally, we will assess the extent and nature of shared decision making through a review of audio-recordings of the patient encounters with their providers.

### Study Population

#### Setting

This study will take place at the cardiology practice of an academic, tertiary care health system in central Massachusetts.

#### Providers

We will enroll up to 20 cardiology providers practicing at the University of Massachusetts (UMass) Memorial Healthcare System in the Ambulatory Care Center (ACC) Cardiology Clinic.

#### Patients

We will enroll up to 60 patients who are not receiving AC therapy, with each provider contributing up to 6 AF patients with elevated stroke risk. Recruitment will be restricted to patients aged 18 years and older. To identify patients, we will use a diagnostic concept grouper within our electronic health record (EHR) system that follows our inclusion criteria consistent with AF. Subsequently, patients will be filtered to retain those patients with CHA_2_DS_2_-VASc stroke risk scores of 2 or greater [8] who were not on AC therapy and had an upcoming cardiology visit in the next 3 months. The CHA_2_DS_2_-VASc score assigns 1 point for congestive heart failure, hypertension, age 65 to 74 years, diabetes mellitus, vascular disease history, and female sex. The score assigns 2 points for age greater than 75 years and for previous stroke or transient ischemic attack history.

The following participants will be excluded: patients that have a WATCHMAN device or have had left atrial appendage closure surgery, patients in hospice or for whom life expectancy is less than 6 months, and patients with bleeding episodes or falls with injury 4 weeks prior to their cardiology appointment. Additionally, patients with preferred languages other than English will be excluded from the study because the app AFib 2gether is only available in English. Patients will be excluded from the study if they are members of vulnerable populations (ie, pregnant women and prisoners). The eligibility process is outlined (see Figure 1) to represent how patient eligibility will be verified before patients consent to participate in the study.

**Figure 1 figure1:**
[figure not shown]
Overview of the provider and patient eligibility process for consent and enrollment in the study.

### Study Procedures

#### Screening and Recruitment

A custom query developed by the information technology department at our institution will be used to identify eligible patients who have encounters with consenting cardiology providers in the upcoming 3 months. A manual review of patients’ charts will be conducted to confirm that a patient was not receiving AC therapy (eg, from an outside provider, sometimes documented in scanned notes as opposed to structured variables).

The research assistant (RA) will start recruiting providers who had 3 or more patients that fit the study inclusion criteria. Each provider will then receive a study inquiry email from the RA to see if they are interested in participating in the study. If the provider agrees, they will sign the consent form and a letter will be mailed to their patients. Once enrolled, providers will receive a link to the secure REDCap (Research Electronic Data Capture)-based survey [10] to self-administer a questionnaire (see Multimedia Appendix 1) about their knowledge regarding AF management.

Additionally, letters signed by the patient’s cardiology provider along with a fact sheet and Health Insurance Portability and Accountability Act (HIPAA) authorization form will be mailed to each eligible patient 1 to 2 weeks prior to the patient’s appointment. Approximately 5 days later, the RA will call patients for a follow-up to gauge interest in participating in the study. For patients who scheduled a visit within 1 week of the appointment date, messages with study recruitment and consent materials will be sent to the patients as attachments using the Epic patient portal. Subsequently, patients will be called in the next 1 to 2 days to obtain consent. For patients who did not respond to either of these mechanisms or for patients that were scheduled within 24 hours of their appointment, our Institutional Research Board approved the RA to meet and recruit patients, as feasible, in the waiting room of the cardiology clinic prior to the patient visits.

#### Intervention and App Description

Once a patient has provided informed consent to participate, we will ask them to download the AFib 2gether mobile app onto their personal smartphone or a family member’s smartphone or to use the study device for in-person visits. AFib 2gether is a mobile app that may be helpful to foster a shared decision-making discussion between patients and providers. The AFib 2gether app may help increase a patient’s understanding of their risk of stroke due to AF through the personalized stroke risk calculator, information sheets, videos, website links, and facts in the app (see Figure 2). In addition, the app allows patients to select questions about AF and their stroke risk score to discuss with their health care providers. The goal of the app is to improve patient understanding; it stands in distinction to other apps related to assisting providers with choosing a particular anticoagulant.

For patients recruited at the time of their office visit, the RA will offer the study smartphone, an Android OS smartphone, for patient use with the AFib 2gether app predownloaded on the device or will assist the patient in downloading the app onto their personal device. Next, the RA will instruct the patient to put in a study-specific code for the app. Once the patient puts in the study code, the patient will be able to consent to the app’s terms and conditions. Once the patient has agreed to the app’s terms and conditions, the patient may then answer questions on the app to determine their knowledge of their stroke risk score. The questions include whether the patient has ever had heart failure, hypertension, diabetes, stroke, vascular disease, or previous stroke and what their age and gender are. Once the participant answers the questions, the app will display their categories for stroke risk and will allow the participant to select up to three questions from a list of 13 commonly asked questions that they may want to discuss with their provider during their visit based on their risk assessment. Examples of the types of questions a participant could choose are as follows: Would you like to know more about your condition? What is the cost of AC therapy? and What are the benefits of going on AC therapy to avoid stroke? The participant will be given the option to type in any additional questions they may have that were not listed in the app. Lastly, the patient’s risk factors and questions will then be sent via email to the provider as a PDF document to review prior to their appointment.

**Figure 2 figure2:**
[figure not shown]
Advertisement of the AFib 2gether app in the Heart Rhythm Society’s patient toolkit with screenshots of sections of the app.

#### Data Collection

The RA will administer a modified version of the Mobile App Rating Scale (MARS) for the purpose of assessing usability (see Multimedia Appendix 2) [11]. The MARS is a validated survey that can be used to assess health apps [11]. The modified questionnaire includes functionality and aesthetics domains that are similar to the original. We will not include items from the engagement and entertainment or information domains. We will include one item from the app subjectivity quality domain, which is the overall star rating of the app. This followed recent evidence suggesting the validity of scoring each domain separately [12]. The RA will wait with the participant until their visit with the provider begins. Once the cardiology provider is ready to begin the visit, the RA will then turn on and place the encrypted recorder—the Olympus DS-7000 (OM Digital Solutions)—in the room. At this point, the RA will prompt the provider to review the questions posed by the patient and then step outside the room and allow the visit to take place without any further scripting.

At the end of the visit, the RA will collect the voice recorder and administer questionnaires to both the patient and provider related to the perceived usefulness of the app following the technology acceptance model (TAM) [13,14]. Although we did also consider the unified theory of acceptance and use of technology 2 (UTAUT2), which unifies the eight theories including the TAM, we selected the TAM as our theoretical construct given its applicability to individual patients following other examples in the literature. Accordingly, we will administer a questionnaire assessing the patient perceived usefulness of the mobile app (see Multimedia Appendix 3). For providers, we will administer a questionnaire assessing the provider perceived usefulness of the mobile app (see Multimedia Appendix 4).

Once the patient completes their appointment and questionnaires, the RA will give the patient a US $25 Amazon gift card for participating in the study. Providers will be compensated with a US $200 Amazon gift card after they complete all study activities.

The UMass Medical School approved our protocol, including data collection and incentive procedures.

#### Modified Study Procedures for COVID-19

During periods when in-person recruitment is not permissible due to COVID-19 restrictions, we will utilize remote recruitment and consenting processes. For remote patient recruitment, the same provider letter will be used, but the fact sheet and HIPAA authorization will be modified to remove information about the audio-recording. We will not replace audio-recording with another method of objectively measuring the extent and type of shared decision making that occurs. The original HIPAA authorization form’s wet signature will be replaced with a process of acknowledgment to disclose protected health information through the process of agreeing to participate in the study and phone interview.

### Primary Outcomes

#### Usability

We will group items in the MARS into three domains for functionality, aesthetics, and overall quality; they will receive a rating of number of stars out of 5.

#### Perceived Usefulness

Perceived usefulness will be calculated for patients and providers based on a custom set of questions derived from the TAM. More specifically, we will examine their distribution similar to how we described the usability outcome. We collected usefulness data on a 5-point Likert scale for simplicity’s sake, in contrast to the traditional 7-point Likert scale used in TAM or UTAUT2 literature. In addition, timing will be recorded for each of the components of the shared decision-making encounter. The distribution of time required for each activity will be reviewed.

#### Shared Decision Making

We will also assess for elements of shared decision making, including multiple themes covered in established instruments [15]. These will include a mention that options are available, evidence that the provider shared stroke and bleeding risk with the patient, and, most notably, evidence of patient involvement in the discussion.

### Secondary Outcome: Anticoagulation Start

The RA will review each patient’s medical record in our institution’s EHR system, Epic, to see if the patient started AC therapy within these 6 months.

### Patient and Provider Characteristics

#### Patient Demographics

Through electronic capture from the data repository associated with our institution’s EHR system, we will collect age, sex, race, and ethnicity information.

#### Comorbidities

From our EHR system, we will also collect the CHA_2_DS_2_-VASc scores using our previously validated algorithm. From manual chart review, we will also collect information about why the patient did not previously receive AC therapy, including potential responses, such as *low AF burden*, *the patient refused*, *fall risk*, and *concomitant aspirin use*.

#### Provider Factors

Through information available from our credentialing office, we will collect provider age and years in practice in addition to provider credentials (ie, MD versus NP or PA).

#### Provider Knowledge

We will measure provider AC therapy decision-making confidence in several areas, including applying guidelines from the ACC, the AHA, and the Heart Rhythm Society and assessing antithrombotic therapy, using CHA_2_DS_2_-VASc scores to access stroke risk, among others. Response options will include *somewhat confident*, *moderately confident*, and *very confident*.

### Analysis

For each domain of usability of the app (ie, MARS items), we will calculate the mean and standard deviation. For perceived usefulness, we will group patients into consolidated ordinal categories based on the Likert response format. We will then assess for trends in associations and examine associations between patient characteristics and usability and perceived usefulness. Where feasible, given low sample size, we will also calculate *t* tests or chi-square tests for determining statistical significance. We will perform all analyses in SAS 9.4 (SAS Institute Inc) [16]. The UMass Medical School Institutional Review Board approved our protocol.

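### Merging the 5-point usefulness answers and testing them by chi-square gives up power that an ordinal or rank analysis of all five levels would keep

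*Protocol article*

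**What the plan says.** Under Primary Outcomes, the Perceived Usefulness section covers both groups of respondents: "Perceived usefulness will be calculated for patients and providers". The answers are recorded in full: "We collected usefulness data on a 5-point Likert scale". Of these items it says "we will examine their distribution similar to how we described the usability outcome".

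The Analysis section then sets the handling: "For perceived usefulness, we will group patients into consolidated ordinal categories based on the Likert response format". Neither the number of categories nor the cut-points are given. It continues: "We will then assess for trends in associations and examine associations between patient characteristics and usability and perceived usefulness". For significance it names only t "tests or chi-square tests for determining statistical significance", under the condition "Where feasible, given low sample size". It names no rank, trend or exact test and gives no criterion for feasibility.

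The sample is capped in the Patients section: "We will enroll up to 60 patients who are not receiving AC therapy".

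**The concern.** The stated aim and the named test do not match. The plan calls the categories ordinal and wants trends. The natural test for a grouped outcome against a categorical characteristic, among those it names, is Pearson's chi-square. With three or more levels that test gives the same result however the levels are ordered, so it spends its degrees of freedom on patterns that nobody is asking about. Before that, merging has already removed distinctions that the patients made.

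In a large study neither step would matter much. With at most 60 patients, the study can detect only strong associations with usefulness, and both steps reduce what it can detect. The full answers are collected anyway, so the loss can be avoided.

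**Working it through.** **No figure to reproduce.** The protocol gives no alpha, effect size, power or expected answer distribution. Taken from the document: five levels and at most 60 patients. Assumed here: the answer spreads, the cut-points, the group splits, an odds ratio of 3 and a two-sided 5% level.

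**Step 1: information kept after merging.** For a two-group comparison under proportional odds, information is proportional to 1 − Σp³, where p are the level shares. For an assumed spread of 5/10/20/40/25%:

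- Five levels: 1 − (0.000125 + 0.001 + 0.008 + 0.064 + 0.015625) = 0.911.
- Three levels (1-2 | 3 | 4-5, shares 15/20/65%): 1 − (0.003375 + 0.008 + 0.274625) = 0.714. The ratio is 0.714/0.911 = 0.784, a loss of about 22%; 60 × 0.784 ≈ 47 patients.
- Two levels (1-3 | 4-5, shares 35/65%): 1 − (0.042875 + 0.274625) = 0.683. The ratio is 0.749, a loss of about 25%; 60 × 0.749 ≈ 45 patients.

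**Step 2: range over other assumptions.** The same formula gives:

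- Even answers (20% each): five levels 0.96. Three levels (40/20/40%) 0.864, loss 10%. Two levels (60/40%) 0.72, loss 25%.
- Moderate skew (5/10/25/35/25%): five levels 0.925. Three levels (15/25/60%) 0.765, loss 17%. Two levels (40/60%) 0.72, loss 22%.
- Strong skew (7% in the bottom two levels, then 13/40/40%): cut 1-2 | 3 | 4-5, loss 44%. Cut 1-2 | 3 | 4 | 5, loss 0%.
- Ceiling (5% in the bottom two, then 5/30/60%): cut 1-2 | 3 | 4-5, loss 64%. Cut 1-4 | 5, loss 5%.
- Symmetric (10/20/40/20/10%): cut 1-4 | 5 gives 0.27/0.918 = 0.294, loss 71%. Cut 1-2 | 3 | 4-5, loss 4%.

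So the loss runs from 0% to about 71%, depending on where the answers fall and where the cuts are placed.

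**Step 3: power.** There were 20,000 simulated tables per scenario, with 30 patients per group. One group has the assumed spread; the other is shifted towards agreement by an odds ratio of 3.

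| Assumed answers | Wilcoxon, 5 levels | Trend test, 3 levels | Chi-square, 3 levels | Chi-square, 2 levels |
|---|---|---|---|---|
| Even | 0.65 | 0.59 | 0.48 | 0.56 |
| Moderate skew | 0.62 | 0.45 | 0.36 | 0.47 |
| Strong skew | 0.58 | 0.26 | 0.17 | 0.29 |
| Ceiling | 0.47 | 0.11 | 0.04 | 0.15 |

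The moderate-skew row separates the two causes. Using order on three levels raises power from 0.36 to 0.45, and keeping all five levels raises it to 0.62.

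The gap narrows with uneven groups. Under moderate skew, Wilcoxon against chi-square on three and two levels is 0.51 against 0.39 and 0.44 at 15/45, and 0.41 against 0.35 and 0.35 at 10/50. It also narrows, without reversing, when the shift at 30/30 is away from agreement.

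**Step 4: sparse cells and test size.** At 30/30 with three levels, the smallest expected count is 30 × 0.15 = 4.5 under moderate skew and 30 × 0.07 = 2.1 under strong skew. The actual size of the nominal 5% chi-square on merged data was 0.025 to 0.057 across the scenarios.

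**The case against.** Much can be said for the plan.

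- **The aim is descriptive.** The study measures usability and usefulness in one arm, and the association tests are an addition. This stands: the power figures concern those tests only. The five-point data remain available, so the grouping is reversible.
- **Order is not forgotten.** The categories are called ordinal and trends are to be assessed. A reader might infer that the plan ignores ordering altogether. It does not. Only the chi-square test does so, and with two categories there is no further order to use. The plan also does not say which test goes with which outcome; pairing chi-square with the grouped usefulness answers is the natural reading, not a stated one.
- **Testing is conditional on feasibility, and merging reduces sparseness.** A reader might infer that the P values would be unreliable. The simulated sizes do not support that: the errors are mostly conservative and the cost is power. The unmerged five-level table is sparser still, with an expected count below 5 in 80–100% of simulated tables. That argues against an ordinary chi-square on five levels, not against a rank or ordinal test.
- **Multiplicity.** A reader might infer that many chance findings are certain. The number of tests is not stated, and a rule may sit in an analysis plan that is not shown. If tests were independent at 5%, the chance of at least one false positive would be 1 − 0.95^k: 23% for 5 tests, 40% for 10 and 64% for 20. This supports an exploratory label and no more.
- **Consistency between sections.** A reader might infer that Perceived Usefulness and Analysis prescribe conflicting analyses. The former speaks of examining a distribution and does not mention a mean and standard deviation, so grouping afterwards is compatible with it. That the grouping sentence mentions only patients may be condensation.

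**Conclusion.** The point holds as a matter of method and power. The Analysis section commits to merging a five-point primary outcome and names for significance only tests that, in the natural pairing, use neither the full scale nor the order it says it wants. A better method is available at almost no cost.

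No single percentage can be given for the loss, because the protocol fixes neither the answers nor the cut-points; a flat statement that a quarter is lost would describe one assumed case. All figures rest on the assumptions listed above and treat patients as independent. Clustering of up to 6 patients per provider was not modelled.

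**What to change.** In the Analysis section, replace the chi-square on merged categories with an analysis of all five levels. Two routes would serve:

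- a Wilcoxon or ordinal trend test, with exact P values when expected counts are small; or
- a proportional-odds model with provider-clustered standard errors.

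These should be kept as alternatives. Standard exact rank and trend tests assume independent observations, so they cannot simply be run with clustering by provider.

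Report the full five-level distribution for patients and for providers separately, and use merged categories for display only. Label the associations with patient characteristics as exploratory and give each with a 95% confidence interval.

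The cost is a change of wording and slightly more analysis work, with no new data. Fewer results could be called significant.

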## Discussion

We have developed a protocol to measure the usability and perceived usefulness of a mobile app to facilitate shared decision making for patients with AF not currently receiving AC therapy. We also describe the administration of a separate provider survey that will allow us to measure the association between provider knowledge and each of these outcomes. Our protocol provides flexibility to recruit patients during the COVID-19 pandemic or other circumstances where face-to-face interaction is not possible and where telehealth virtual engagement strategies are implemented.

With the fast-growing use of online sources for accessing health information throughout society, a shared decision-making app or tool for clinical settings has a great potential for impact. Man-Song-Hing et al developed a decision aid based on a risk stratification scheme that helped patients and providers make informed decisions about whether to use warfarin compared with aspirin for patients with AF [17]. More patients in the intervention group (n=138, 99%) were able to make definite choices regarding antithrombotic therapy compared with those in the control group (n=139, 94%; *P*=.02). More recently, Kunneman et al tested a shared decision-making tool that provided individualized risk estimates of stroke in various AC therapy options [18]. Although they did not find a significant effect on treatment decisions, more clinicians were satisfied with the encounter in the intervention arm compared with the standard arm. Neither of the two studies specifically studied the usability or perceived usefulness of their shared decision-making tool [17,18].

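### The only significance tests named assume independent observations, although patients and apparently repeated provider ratings are nested within about 10 to 20 providers; P values for provider-level factors would be too small if encounters are the unit of analysis.

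*Protocol article*

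**What the plan says.** On the layout, the Providers section states "We will enroll up to 20 cardiology providers", and the Patients section states "We will enroll up to 60 patients who are not receiving AC therapy, with each provider contributing up to 6 AF patients". Under Screening and Recruitment, the research assistant "will start recruiting providers who had 3 or more patients that fit the study inclusion criteria", so providers with several study patients are expected by design.

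On measurement, the Data Collection section has the research assistant, when the visit ends, "administer questionnaires to both the patient and provider related to the perceived usefulness of the app". The natural reading is one provider form per encounter, although the article does not say so outright. The provider knowledge questionnaire is filled in by the provider after enrolment, so it describes the provider and not the encounter.

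On analysis, the plan is mainly descriptive: means and standard deviations for the usability domains, and ordinal categories for perceived usefulness. It will then "examine associations between patient characteristics and usability and perceived usefulness" and, if the small numbers allow, add t "tests or chi-square tests for determining statistical significance". The Discussion says that the provider survey will "allow us to measure the association between provider knowledge and each of these outcomes". The article does not mention clustering, repeated measures, a mixed model, GEE or robust standard errors, and non-independence is not among the limitations it lists.

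**The concern.** Patients of the same provider may give similar usefulness ratings because they had the same provider's conversation. Several ratings by one provider are repeated measures on one person. A t test or chi-square test on encounter-level rows ignores both.

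The consequence is clearest for anything that varies only between providers. Provider knowledge takes one value per provider, so the sample size for that question is 20 or fewer. Treating it as 60 gives too small a standard error and too many false positives. The article presents the study as groundwork for a multicentre randomized trial, so a spurious provider-knowledge effect, or provider usefulness reported as if 60 independent raters had answered, could mislead that trial's design.

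**Working it through.** The article states no power, alpha or sample-size derivation, so there is no figure of its own to reproduce.

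**Inputs from the article.** At most 20 providers (Providers); at most 60 patients and at most 6 per provider (Patients). Two layouts bracket the design: 60/20 = 3 patients per provider, and 60/6 = 10 providers if all reach the cap.

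**Assumptions.** Two-sided nominal alpha of 0.05; equal numbers of patients per provider; ICC of 0.01 to 0.20 for patient ratings and up to 0.5 for one provider's repeated ratings. None of these is stated in the article.

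**Formulas, for a factor that varies only between providers.** With m patients per provider, the design effect is DE = 1 + (m − 1) × ICC. The effective sample size is 60/DE. The real error of the ordinary test is 2 × [1 − Φ(1.96/√DE)].

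Example: for m = 6 and ICC = 0.20, DE = 1 + 5 × 0.20 = 2.0, the effective size is 60/2.0 = 30, and the real error is 2 × [1 − Φ(1.96/1.414)] = 0.166.

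| Layout | ICC | DE | Effective n | Real error (formula) | Simulated t test |
|---|---|---|---|---|---|
| 20 × 3 | 0.01 | 1.02 | 58.8 | 0.052 | not run |
| 20 × 3 | 0.05 | 1.10 | 54.5 | 0.062 | 0.062 |
| 20 × 3 | 0.10 | 1.20 | 50.0 | 0.074 | 0.072 |
| 20 × 3 | 0.20 | 1.40 | 42.9 | 0.098 | 0.100 |
| 20 × 3 | 0.50 | 2.00 | 30.0 | 0.166 | 0.175 |
| 10 × 6 | 0.01 | 1.05 | 57.1 | 0.056 | not run |
| 10 × 6 | 0.05 | 1.25 | 48.0 | 0.080 | 0.081 |
| 10 × 6 | 0.10 | 1.50 | 40.0 | 0.110 | 0.106 |
| 10 × 6 | 0.20 | 2.00 | 30.0 | 0.166 | 0.168 |
| 10 × 6 | 0.50 | 3.50 | 17.1 | 0.295 | 0.317 |

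The simulation used 20,000 runs per scenario, a random provider effect and a binary provider factor split evenly. The chi-square test on dichotomised scores is affected less: in the 10 × 6 layout it gave 0.130 at ICC 0.20 and 0.245 at ICC 0.5. A t test on provider means gave 0.049 to 0.051 in every scenario.

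**Patient characteristics, ordinary t test, outcome ICC 0.05 to 0.5.**

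- Characteristic unrelated to provider: 0.049 to 0.054 in both layouts, so essentially no inflation.
- Characteristic balanced within provider (10 × 6 only): 0.043, 0.044, 0.031 and 0.010 at ICC 0.05, 0.1, 0.2 and 0.5, so P values are too large.
- Characteristic that itself clusters by provider (assumed ICC 0.2): 0.052 to 0.075 (20 × 3) and 0.056 to 0.106 (10 × 6).

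**The case against.** A reader might infer that all P values in this study will be too small. The article does not support that. Its sentence on t and chi-square tests follows associations with patient characteristics, for which the ordinary test is close to 5%, or conservative, unless the characteristic clusters by provider.

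A reader might also take the 17–30% error as a property of the plan. It needs a provider-level factor, an assumed ICC of 0.5 and a test on encounter-level rows. The Analysis section assigns no test to provider factors, and the Discussion names neither a test nor a unit for the provider-knowledge association. A test on one row per provider would be consistent with the text. The link is therefore an inference, drawn because no other significance test is named.

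Usability is probably the least exposed outcome. In the sequence under Data Collection, the patient completes the app rating scale before the visit starts, so that encounter cannot shape the score. The planned means and standard deviations of patient ratings are not biased by clustering, and a standard deviation makes no claim of precision. The tests are additional and conditional, in a single-arm study with no stated hypothesis.

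All of this stands, and it limits the scope and severity. It does not remove the point. A fuller protocol or analysis plan may handle clustering, but the article does more than stay silent: it names methods that assume independence for a design that is visibly nested, and promises an association whose exposure exists only at provider level.

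**Conclusion.** The point holds in a limited form, at moderate severity. The named tests do not match a design with about 10 to 20 clusters. If they are applied to encounter-level rows, P values for provider-level factors are too small: real error of about 6–10% (20 × 3) or 8–17% (10 × 6) at ICC 0.05–0.20, and about 17–30% by formula at ICC 0.5 for repeated provider ratings. At ICC 0.01 the error is 5.2–5.6%, which is negligible.

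For patient characteristics the tests are miscalibrated in either direction or not at all, with real error of about 5–11% where the characteristic clusters by provider. These sizes rest on ICCs that the article does not give, on equal cluster sizes, on one provider form per encounter, and on the inference that the named tests would also be used for provider factors.

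**What to change.** In the Analysis section:

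- Name the provider as the cluster, and state whether providers complete the usefulness form after every encounter.
- Analyse provider-level factors, including provider knowledge, and provider usefulness ratings on one summary row per provider, with n of 20 or fewer stated as the sample size. In the check above this restored the error to about 5%.
- Where associations with patient characteristics are tested, use a method that accounts for provider, for example a random provider intercept, or GEE with a small-sample correction. If such a model cannot be fitted with so few clusters, report the association descriptively without a P value.

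The cost is a change of wording and slightly more analysis work, with less favourable P values for provider-level factors. Recruitment, questionnaires and visits do not change.
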